#### Treatment cessation

As part of the interdisciplinary treatment programme, clinicians will have ongoing communication with each other throughout the participant’s individualised treatment (communication between clinicians will be documented). Participants may be discharged from treatment early based on clinical opinion. They may be discharged from one discipline before the other (e.g. if physical issues resolve, they would be discharged from physiotherapy yet may continue psychological intervention to address persisting cognitive, mood, or behavioural issues).

#### Relevant concomitant care and interventions

Participants may undergo concomitant care and interventions for comorbid conditions. Concomitant treatments will be documented at the start of the trial. Parallel treatments for concussion will not be permitted during the trial.

### Qualitative guide to explore participant experiences of i-RECOveR

This mixed-methods study will also qualitatively explore participant experiences of i-RECOveR.

#### Participant experience

To elicit the participant’s experience of their PPCSs and the intervention, the following interview guide will be utilised in semi-structured interviews:What was your *experience* of the intervention?What were the *most helpful elements* of the intervention?What were the *least helpful elements* of the intervention?How has the intervention changed the way you think about your concussion?Compared to how you were before the intervention, what *effects have you noticed on your life* since completing the intervention?What effects have you noticed on your *primary complaint* (e.g. mood/cognition/headaches)?Was there anything else you would like to say about the intervention?

### Data analysis plan

#### Data management plan

All data will be deidentified and stored securely on REDCap. Prior to the commencement of data collection, a REDCap database will be established. Where applicable, range checks for data values will be embedded into the database. To mitigate missing data, all items of a measure must have a value entered for the measure to be marked complete. Throughout the trial, data audits will be completed by two researchers, and all items for questionnaires will be double scored.

##### AIM 1: Feasibility of i-RECOveR

Data on recruitment and retention rates, protocol compliance, adverse events, treatments received, and treatment acceptability will be collected and analysed descriptively to inform guidelines for progressing the pilot trial to a larger phase 2 trial [25. ]. Adequate completion rates (i.e., 75%), limited adverse events, and signs of preliminary efficacy will inform whether the trial will progress to a randomised controlled design.

**Treatment fidelity**

Psychology treatment sessions will be audio recorded to allow for analysis of treatment fidelity. Recordings of 10% of the sessions will be rated by an independent psychologist, evaluating adherence to the treatment protocol. For physiotherapy and medical treatments, fidelity will be assessed by auditing clinical notes and evaluating whether the treatment modules have been completed.

##### AIM 2: Preliminary efficacy of i-RECOveR

**Post-concussion symptom severity**

Participant-reported post-concussion symptoms (RPQ) will be graphed to allow for visual inspection using GraphPad Prism 8. Systematic visual analysis will be conducted in line with established guidelines proposed by Spriggs, Lane, and Gast [101. ] and Lane and Gast [52. ], incorporating both within- and between-phase analyses to evaluate trend, level, and stability of data. Trend will be assessed using the split-middle method using median values [52. ].

Statistical analysis of single-case experimental data (i.e. total RPQ scores collected three times a week) will be conducted to augment visual analysis to provide more robust conclusions about the dataset. Planned comparisons between baseline and intervention phases will be conducted using the non-overlap method, Tau-U [68. ]. Tau-U is a nonparametric approach, appropriate for small data sets, which controls for improving trends (whether linear, curvilinear, or mixed) in the baseline phase and autocorrelation to generate an effect size [113. ]. An online Tau-U calculator (http://www.singlecaseresearch.org/calculators/tau-u) will be used to check for trend in the baseline, adjust for it where necessary, and calculate contrasts between phases [113. ]. This calculator will also be used to test omnibus statistics.

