### Randomisation

A block randomisation method will be used to randomise participants into baseline duration phases of 2, 4, or 6 weeks. The following website will be used to facilitate randomisation https://www.random.org/lists/. Allocation concealment will be ensured by an independent research assistant to ensure that the research and treatment teams are adequately blinded to baseline phase duration. Allocation into baseline phases will be communicated to participants after all baseline (T1) measures have been completed.

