##### Baseline phase

Once randomised and informed of length of baseline phase, participants will complete the RPQ three times a week on a Monday, Wednesday, and Friday. They will receive the RPQ as a REDCap link via email at 8:00 am and will receive a reminder email at 5:30 pm on the same day if they have not completed the RPQ. If participants do not complete the RPQ after the email reminder, they will be sent a follow-up text message reminder at 8:00 pm. If no response is made after the 8:00 pm reminder, this data point will be noted as incomplete.

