##### Intervention phase

As in the baseline phase, participants will complete the RPQ three times a week on Monday, Wednesday, and Friday and will be provided with reminders as outlined above.

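### Tau-U does not control for autocorrelation as the protocol states, so the omnibus test on RPQ scores taken three times a week is anti-conservative

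*Protocol article*

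**What the plan says.** The analysis is set out in the Protocol article, Data analysis plan, AIM 2, under Post-concussion symptom severity. Visual analysis comes first, and a statistical analysis "will be conducted to augment visual analysis to provide more robust conclusions about the dataset". The method is named there: "Planned comparisons between baseline and intervention phases will be conducted using the non-overlap method, Tau-U". It is described as one "which controls for improving trends (whether linear, curvilinear, or mixed) in the baseline phase and autocorrelation to generate an effect size".

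An online calculator "will be used to check for trend in the baseline, adjust for it where necessary, and calculate contrasts between phases". It has one further task: "This calculator will also be used to test omnibus statistics". Baseline trend is the only adjustment assigned to it. No other step for serial dependence appears, such as pre-whitening, an autoregressive error model or a randomisation test.

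The readings are closely spaced. In the baseline phase "participants will complete the RPQ three times a week on a Monday, Wednesday, and Friday", and the Intervention phase section repeats the schedule: "participants will complete the RPQ three times a week on Monday, Wednesday, and Friday". The Randomisation section says a block method will "randomise participants into baseline duration phases of 2, 4, or 6 weeks".

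**The concern.** The sentence makes a definite claim about a property of the method. It is not a detail left to a later document. If the claim is wrong, two things follow.

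First, consecutive symptom scores from one person two or three days apart are likely to be positively correlated. A variance that treats them as independent is then too small, and tests and intervals built on it look more certain than they are.

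Second, the sentence tells analysts and readers that the problem has been dealt with, so nobody has a reason to check it. The statistics are meant to make the conclusions firmer than visual inspection alone. Under AIM 1, early indications of efficacy are one of three inputs to the decision on a randomised trial, beside completion rates and adverse events.

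**Working it through.** **Inputs from the protocol**
- Baseline readings: 2, 4 or 6 weeks × 3 per week = 6, 12 or 18.
- Intervention readings: up to 12 weeks × 3 per week = up to 36. Early discharge is allowed, so 18 was also tried.
- Participants: 5 replications × 3 tiers = 15, which reproduces the planned sample size. The shortest phase has 6 readings, above the stated minimum of five.

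**Assumptions not in the protocol**
- Two-sided nominal 5% level.
- Lag-1 correlation from 0 to 0.7.
- Omnibus statistic taken as the inverse-variance weighted mean of the 15 Taus.

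**Step 1. Does the statistic contain a term for autocorrelation?** With nA baseline and nB intervention readings, S is the number of improving minus worsening baseline–intervention pairs, and

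Tau = S / (nA × nB), SE(Tau) = √[(nA + nB + 1) / (3 × nA × nB)].

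The standard error depends only on the two counts:
- nA = 6, nB = 36: √(43/648) = 0.258
- nA = 12, nB = 36: √(49/1296) = 0.194
- nA = 18, nB = 36: √(55/1944) = 0.168

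These values are the same whatever the correlation. The contrast does not see order within the intervention phase either: shuffling those readings removes their autocorrelation and leaves S unchanged. The trend correction subtracts the baseline's own count of ordered pairs (S minus S within baseline). That removes monotone drift in the baseline and is not a correction for serial dependence.

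**Step 2. How large is the effect?** Null series were simulated as stationary AR(1) scores with SD 5, rounded and limited to 0–64, with no trend and no treatment effect. There were five participants per tier, 36 intervention readings and several thousand trials per setting. Rejection rates at nominal 5%:

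| Lag-1 correlation | One participant | Omnibus, 15 participants | True SD ÷ stated SE (omnibus) |
|---|---|---|---|
| 0 | 4–6% | 5–6% | 1.0 |
| 0.1 | 7% | 7–8% | 1.1 |
| 0.2 | 9–11% | 9–11% | 1.2 |
| 0.3 | 12–15% | 13–14% | 1.3 |
| 0.5 | 21–25% | 22–24% | 1.6 |
| 0.7 | 33–40% | 34–35% | 2.0 |

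Some variants of the trend correction fell a few points outside these ranges. None removed the inflation, and 18 intervention readings gave similar results.

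**Step 3. Cross-check by hand.** If the true SD is r times the stated SE, the rejection rate is 2[1 − Φ(1.96/r)]:
- r = 1.2: 2[1 − Φ(1.63)] ≈ 10%
- r = 1.3: 2[1 − Φ(1.51)] ≈ 13%
- r = 1.6: 2[1 − Φ(1.23)] ≈ 22%
- r = 2.0: 2[1 − Φ(0.98)] ≈ 33%

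These agree with the table. Pooling does not dilute the problem, because every participant's variance is understated by a similar factor. For the same reason the result does not hang on the assumed weights: any fixed weighting of the 15 Taus inherits an inflation between the smallest and largest participant-level values.

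**Step 4. Does an alternative hold its level?** A one-sample t-test on the 15 participant Taus (14 degrees of freedom) rejected in 5–6% of the same null trials at every correlation. The participant is then the unit, and within-person correlation shows up in the observed spread.

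**Step 5. Is the estimate affected?** No. The mean Tau stayed centred on zero at every correlation. The error lies in the standard error and whatever is built on it.

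**The case against.** The case for leaving this alone rests on its setting. This is a feasibility pilot whose primary outcomes are recruitment, retention, compliance and adverse events. Tau-U supports visual analysis, and the disputed sentence is about an effect size. The protocol states no significance level, does not promise participant-level p-values or Tau-U intervals, and sets no significance threshold for progression. All of that stands and limits the weight of the point. It does not rescue the sentence, and an omnibus test is inferential.

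Several stronger readings are tempting but not supported:

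- **That the inflation is known to be severe.** The protocol gives no RPQ autocorrelation. At 0.1 the excess is two to three percentage points; at 0.7 it is about 30.
- **That almost every null trial would yield a significant participant.** At a correlation of 0.5, at least one of 15 tests is significant in about 98% of null trials. But 15 perfectly calibrated tests would already give 1 − 0.95^15 = 54%, and the protocol nowhere counts one significant participant as success.
- **That the pooling is itself an error.** Under the assumed weighting, the 6-week tier counts for more than the 2-week tier: 1/0.168² = 35 against 1/0.258² = 15. Giving longer series more weight is ordinary practice and does not bias a null test, and the protocol does not describe the weighting. Differences between participants in individualised treatment play no part in the rates above.
- **That a randomisation test must supply the p-value.** Permuting baseline lengths within blocks of three had power of 76–94% for an immediate 1-SD step, but only 6–8% for gradual improvement reaching 2 SD by week 12. Gradual change is plausible in a 12-week programme, and the protocol states no block size.

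**Conclusion.** The statement that Tau-U controls for autocorrelation is wrong. That follows from the form of the statistic and needs no assumption about the data. The consequence is an anti-conservative omnibus test, and the same applies to any participant-level p-values or intervals taken from the calculator. The omnibus false-positive rate runs from about 7–8% at a lag-1 correlation of 0.1 to 34–35% at 0.7, against a nominal 5%.

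The size is conditional on the assumed correlation, an AR(1) pattern, a two-sided 5% level and no trend or effect. A reader might infer that the Tau estimates are biased or that the feasibility conclusions are at risk. Neither follows: the estimate stays centred in a stationary series, and the damage is confined to the secondary efficacy aim and the efficacy input to progression. This should be fixed, but it does not undermine the trial.

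**What to change.** 1. Delete the reference to autocorrelation from the description of Tau-U.
2. Keep Tau-U as a descriptive effect size alongside the visual analysis.
3. Replace the calculator's omnibus test with inference from the spread of the 15 participant-level effects (one-sample t, 14 degrees of freedom), or with a mixed model with participant random effects and AR(1) residuals. The t-test was checked above; the mixed model was not simulated and should be checked on series of this length before use.
4. Report the observed lag-1 autocorrelation for each participant, so that readers can judge where the trial falls in the range.
5. A randomisation test based on the allocated baseline lengths may be added as a supplement, with its low power for gradual change stated.

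The cost is a change to the analysis text, with wider intervals and a less favourable p-value where correlation is present. Sample size, assessments and data collection are unchanged.

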**Methods:**

Fifteen individuals with mild traumatic brain injury and PPCSs will receive up to 12 weeks of interdisciplinary treatments including psychology, physiotherapy, and medical interventions. Primary feasibility outcomes including data on recruitment and retention rates and treatment adherence will be explored descriptively. The cognitive therapy rating scale will be used to assess treatment fidelity. A single-case series with multiple baseline design will be used to explore preliminary efficacy. Participants will be randomly assigned to baseline phases of 2, 4, or 6 weeks. Regarding patient-centred secondary outcomes, the Rivermead Post-Concussion Symptoms Questionnaire will be assessed three times a week during baseline and treatment phases. Secondary outcomes also include measures of mood, sleep and fatigue, physical functioning, return to activity, and health-related quality of life. Patient-centred outcomes will be assessed at baseline, pretreatment, post-treatment, and one- and three-month follow-up. Thematic analysis of participant experiences will be explored through qualitative interviews.

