It is clear that further scientifically rigorous work in this area is warranted to evaluate the feasibility and efficacy of interdisciplinary interventions, evaluate dosage, and identify factors that contribute to the effectiveness of such interventions. There is also a need to control for the effects of spontaneous recovery when evaluating the potential efficacy of treatments for concussion. Research trials may address this by establishing baseline rates of symptoms over time before the introduction of treatments. This pilot study, using a single-case series design with multiple baselines, therefore aims to pilot and conduct a preliminary evaluation of an interdisciplinary intervention that incorporates expertise from neuropsychology, physiotherapy, and medicine to target the primary factors thought to contribute to PPCSs. Using a single-case series experimental design principally enables the examination of the appropriateness of the trial design (e.g. choice of outcome and measurement, recruitment protocol, adherence to treatment manual) to inform the design of a subsequent definitive randomised controlled trial as well as enabling the evaluation of preliminary efficacy of this novel treatment.

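### Tau-U is said to control for improving baseline trends of any shape, but on this schedule its correction is only partial, so natural recovery that continues into treatment still scores as an effect

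*Protocol article*

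**What the plan says.** The Introduction sets the requirement: "There is also a need to control for the effects of spontaneous recovery when evaluating the potential efficacy of treatments for concussion". It offers the baseline phase as the means of meeting it.

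Under Data analysis plan, Aim 2 (Post-concussion symptom severity), baseline and intervention phases are compared with Tau-U, which the article says "controls for improving trends (whether linear, curvilinear, or mixed) in the baseline phase". The online calculator "will be used to check for trend in the baseline, adjust for it where necessary, and calculate contrasts between phases", and also supplies the omnibus statistics. No threshold is given for when adjustment is necessary. Tau-U supplements a systematic visual analysis of trend, level and stability, with split-middle trend lines.

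The schedule fixes the number of readings:
- Baseline length: "Participants will be randomly assigned to baseline phases of 2, 4, or 6 weeks" (Abstract, Methods).
- Baseline readings: "participants will complete the RPQ three times a week on a Monday, Wednesday, and Friday".
- Treatment readings: "As in the baseline phase, participants will complete the RPQ three times a week on Monday, Wednesday, and Friday".
- Treatment length: participants "will receive up to 12 weeks of interdisciplinary treatments", but "Participants may be discharged from treatment early based on clinical opinion" (Treatment cessation).

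Under Aim 1, signs of preliminary efficacy are listed with completion rates and adverse events as inputs to the decision to move to a randomised trial.

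**The concern.** Entry is allowed from 4 weeks after injury, when some participants may still be recovering naturally. If symptoms fall steadily through baseline and keep falling at the same rate during treatment, nothing has happened at treatment start, and a method that controlled for the baseline trend should score close to zero. Tau-U does not, because its correction compares baseline readings only with one another. It asks nothing about where the baseline trend would have led. The correction is also weakest where the baseline is shortest, so tiers with identical recovery and no effect can score differently. What is at stake is the RPQ efficacy signal, and through it one part of the progression decision. The feasibility outcomes are untouched.

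**Working it through.** **The plan's own figures.** 5 replications × 3 tiers = 15 participants, as stated. The shortest baseline has 2 × 3 = 6 readings, above the stated minimum of five. The article gives no figure for the size of the trend correction.

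**Inputs.** Baseline readings nA = 6, 12 or 18 (2, 4 or 6 weeks × 3). Treatment readings nB = 36 at most (12 weeks × 3).

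**Formula.** This is the standard definition, which the article does not print. With improvement (falling RPQ) counted as positive, corrected Tau-U = (S_AB − S_A)/(nA × nB). S_AB is the net number of improving baseline-versus-treatment pairs and S_A the net number of improving pairs within baseline. Since S_A cannot exceed nA(nA − 1)/2, the largest correction is (nA − 1)/(2nB).

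**Noise-free straight-line recovery, no treatment effect.** Every pair improves, so S_AB = nA × nB and S_A is at its maximum.

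| Tier | Largest correction, 12 weeks | Corrected Tau-U left | Largest correction, 6 weeks (nB = 18) | Left |
|---|---|---|---|---|
| 2 weeks | 15/216 = 0.07 | 0.93 | 15/108 = 0.14 | 0.86 |
| 4 weeks | 66/432 = 0.15 | 0.85 | 66/216 = 0.31 | 0.69 |
| 6 weeks | 153/648 = 0.24 | 0.76 | 153/324 = 0.47 | 0.53 |

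If the within-baseline pairs are added to the denominator, the 12-week values left are 201/231 = 0.87, 366/498 = 0.73 and 495/801 = 0.62. The conclusion is the same.

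**Single participants with noise, no treatment effect.** These are simulations with 36 treatment readings and independent errors. Slopes and SDs are assumptions, since the article gives none. Entries are for the 2-, 4- and 6-week tiers.

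| Recovery (points/week) | SD | Mean corrected Tau-U | Share with abs(z) > 1.96 |
|---|---|---|---|
| 0 | 3 | about 0 | 4%, 6%, 6% |
| 0.25 | 5 | 0.20, 0.22, 0.22 | 13%, 20%, 28% |
| 0.25 | 3 | 0.32, 0.35, 0.37 | 20%, 43%, 62% |
| 0.5 | 5 | 0.35, 0.40, 0.42 | 26%, 55%, 75% |
| 0.5 | 3 | 0.55, 0.59, 0.62 | 62%, 93%, 99% |
| 1.0 | 5 | 0.62, 0.65, 0.68 | 77%, 98%, 100% |
| 1.0 | 3 | 0.79, 0.80, 0.80 | 98%, 100%, 100% |

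The correction hardly moves the result. At 0.5 points/week and SD 3 the uncorrected means are 0.56, 0.61 and 0.66. Curved recovery to a plateau gave corrected means of 0.75 to 0.93.

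**Pooled omnibus test, no treatment effect.** The simulation has 15 participants, five per tier, with residual SD 4 and inverse-variance pooling, all assumed.
- Mean recovery 0.25 points/week (between-person SD 0.2; 0.25 × 12 = 3 points over treatment on a 0–64 scale): about 96% of trials reject with lag-1 correlation 0.3, and 98% with independent errors.
- Mean recovery 0.5 points/week (between-person SD 0.3), lag-1 correlation 0.3: 100%.
- No trend, independent errors: about 5%.
- No trend, lag-1 correlation 0.3: about 15%.
- Mean slope zero but varying between people (SD 0.2), lag-1 correlation 0.3: 26%.

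Autocorrelation and varying slopes thus account for part of the excess in the correlated case. With independent errors, drift takes the rate from about 5% to 98%.

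**Alternatives, no treatment effect.** A regression on time and phase rejects in 5.7% and 5.2% of trials under straight-line recovery (the 0.25 and 0.5 settings). With recovery that decelerates (assumed 6-week time constant), it rejects in 26% and 61%. In a segmented model fitted per participant, under the same decelerating recovery, the level-change test stays at about 6% while the slope-change test rejects in 12% and 30%.

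**The case against.** Five points on the other side deserve weight.

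- **The wording is narrower than a blanket claim.** It refers to trends in the baseline phase, and subtracting within-baseline pairs is a real adjustment. A reader might infer that Tau-U does nothing about trend. That goes too far: it adjusts partially.
- **Tau-U is not the only safeguard.** Visual analysis looks at trend in both phases, and randomised baselines replicated five times help to expose smooth recovery that does not shift at treatment start. This stands, but neither enters the Tau-U value or its omnibus test, and Tau-U is there to make the visual conclusions firmer.
- **The limits are not absolute.** They assume a complete 12-week phase. Early discharge raises them, as the 6-week columns show. Nor is a large score inevitable: 0.93, 0.85 and 0.76 are the noise-free case, and slow recovery gives individual values of about 0.2 to 0.4.
- **The baseline check.** A reader might infer that six readings can hardly ever trigger the adjustment. The article states neither test nor threshold, so this cannot be shown: with S = 11 of 15, an exact test gives p = 0.056 and a normal approximation 0.039. It matters little, since the limits hold even when the correction is always applied.
- **This is a pilot.** A reader might infer that the progression decision is unsound. The documents do not support that: feasibility is primary, efficacy is one of three inputs, and no Tau-U cut-off is attached to it.

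**Conclusion.** The point holds in limited form. The article credits Tau-U with a control that it provides only in part under this schedule. The limits follow exactly from the stated schedule and the standard formula, given complete data and full-length treatment. The noisy individual values and the omnibus rejection rates depend on assumed slopes, SDs and correlation. They show that modest natural recovery is enough to make the pooled test significant without any treatment effect, not that this trial will report a false result. It should be fixed, but it does not undermine the trial's primary purpose.

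**What to change.** 1. Reword the Aim 2 sentence to say that Tau-U adjusts only partially for baseline trend and does not project it into the treatment phase. Keep Tau-U as a descriptive overlap index.
2. Add, for every participant and without a preliminary trend test, one of two analyses: a segmented model that projects the baseline trend, with the level change at treatment start as the main estimate; or a randomisation test based on the randomised start points.
3. If the segmented model is used, treat the slope change as exploratory, because decelerating natural recovery biases it, and include a sensitivity analysis with a decelerating time scale.
4. Do not cite the 5.7% and 5.2% rejection rates for the segmented model. They belong to the simpler time-plus-phase regression under straight-line recovery.

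The cost is some wording and one further analysis of readings already being collected. The price is wider intervals, especially in the 2-week tier, where six readings say little about the slope.

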## Methods

### Study design

The study will use a single-case series with nonconcurrent multiple baseline A-B design across subjects with 1- and 3-month follow-up post-treatment to examine treatment efficacy and maintenance of gains. The current multiple baseline design will have three tiers, with participants randomly assigned to one of three baselines (2, 4, or 6 weeks) to maximise experimental control [104. ]. The trial will be run as five three-tiered trials to enable replication of trials for the evaluation of external validity [104. ]. The risk of bias in N of 1 trials scale (ROBiNT) and the single-case reporting guideline in behavioural interventions (SCRIBE) will be used to ensure methodological rigour and reporting [102. , 103. ]. Individual and group level data from the single-case studies will be used to examine the feasibility of the intervention to inform the trial design of a phase 2 randomised controlled trial.

We will also explore participant experiences of the intervention using semi-structured interviews and analyse this data using thematic analysis.

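### The protocol says Tau-U controls for autocorrelation; it does not, so its tests are too liberal if the RPQ readings are positively correlated

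*Protocol article*

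**What the plan says.** The point arises in the Protocol article, Data analysis plan, Aim 2, under Post-concussion symptom severity.

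- Role of the statistics: "Statistical analysis of single-case experimental data (i.e. total RPQ scores collected three times a week) will be conducted to augment visual analysis".
- Method: "Planned comparisons between baseline and intervention phases will be conducted using the non-overlap method, Tau-U".
- Property claimed for the method: it adjusts for improving trends "in the baseline phase and autocorrelation to generate an effect size".
- What the online calculator will do: "check for trend in the baseline, adjust for it where necessary, and calculate contrasts between phases". The section adds: "This calculator will also be used to test omnibus statistics".

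The data come from repeated self-report. Under Baseline phase, "participants will complete the RPQ three times a week on a Monday, Wednesday, and Friday", and the Intervention phase keeps the same schedule. Under Aim 1, early evidence of efficacy is one of the considerations in moving to a randomised design, together with completion rates and adverse events.

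**The concern.** Tau-U counts how often readings in one phase lie above or below readings in the other, and it can subtract the monotonic trend within baseline. Neither step estimates or removes correlation between neighbouring readings. The section itself describes only a trend check, a trend adjustment and phase contrasts. It names no step that deals with serial dependence.

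This is therefore a property the method does not have, stated as fact. It is not a detail that could be left to a fuller analysis plan. A reader who accepts the sentence will take the calculator's test results at face value.

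At stake are the phase contrast for each participant and the omnibus test across participants, both on the main patient-centred outcome. The problem would be present even if every participant responded identically, so it is separate from differences in response between participants.

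**Working it through.** **Design figures.** The plan's own sample size reproduces: five replications × three tiers = 15 participants. Baselines of 2, 4 and 6 weeks at three readings a week give nA = 6, 12 and 18, all above the stated minimum of five points per phase. The abstract says participants "will receive up to 12 weeks of interdisciplinary treatments", so nB is at most 12 × 3 = 36. The protocol gives no autocorrelation and no significance level. Lag-1 values of 0.2 to 0.6 and a two-sided 5% level are assumptions.

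**The standard error Tau-U uses.** With S the sum of signs over all nA × nB pairs, the variance under independence is nA·nB·(nA+nB+1)/3. The standard error of Tau is therefore sqrt[(nA+nB+1)/(3·nA·nB)]. With nB = 36:

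- nA = 6: sqrt(43/648) = 0.258
- nA = 12: sqrt(49/1296) = 0.194
- nA = 18: sqrt(55/1944) = 0.168

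Only the numbers of readings enter. No correlation term appears, so the value is the same however dependent the readings are.

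**Null simulation.** Stationary AR(1) series were generated with no trend and no treatment effect, 20,000 per cell. The omnibus is the inverse-variance weighted mean over 15 participants, five per tier. The omnibus and SE-ratio columns span four variants: no trend correction, always corrected, corrected if baseline tau exceeds 0.4 in size, and corrected if baseline trend is significant at 5%. The SE ratio is the actual standard deviation of Tau divided by the one Tau-U assumes, per participant.

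| Lag-1 | Rejection, uncorrected (nA 6/12/18) | Rejection, always trend-corrected (nA 6/12/18) | Omnibus | SE ratio |
|---|---|---|---|---|
| 0 | 4.8 / 5.0 / 4.9% | 4.8 / 5.5 / 5.6% | 4.9–5.4% | 1.00–1.03 |
| 0.2 | 9.4 / 9.8 / 10.5% | 9.2 / 10.4 / 10.9% | 9.9–10.7% | 1.17–1.23 |
| 0.4 | 16.8 / 17.8 / 18.9% | 16.5 / 18.2 / 19.5% | 17.0–18.0% | 1.38–1.49 |
| 0.6 | 27.3 / 30.7 / 30.8% | 26.7 / 31.0 / 31.7% | 27.9–28.5% | 1.66–1.89 |

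**Reading the table.**

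- At zero correlation the test is calibrated, so the inflation comes from the dependence.
- The baseline-trend correction does not remove it.
- Pooling 15 participants does not remove it, because every component variance is understated in the same way.
- Rounding to whole RPQ points at lag-1 0.4 leaves the per-participant rates at 17–20%.
- The mean of the omnibus z stays close to zero. The dependence affects stated precision; it does not shift the effect size under the null.

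**Hand check.** If z has standard deviation k instead of 1, the rejection rate is about 2[1 − Φ(1.96/k)]. For the uncorrected omnibus at lag-1 0.4, k = 1.434, so 1.96/1.434 = 1.367 and the rate is 17.2%, against 17.0% simulated. At 0.6, k = 1.809, so 1.96/1.809 = 1.083 and the rate is 27.9%, against 28.2%.

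**Shorter treatment phases.** Thirty-six readings is a ceiling, because early discharge and missed readings are both allowed for. Repeating the per-participant simulation with nB = 18 gives similar rates: about 9–10% at 0.2, 17–19% at 0.4 and 27–31% at 0.6.

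**The case against.** Four points can be made for the plan.

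1. **No autocorrelation is given, and at zero the test holds its level.** This stands. A reader might infer that the p-values are bound to be too small. The documents do not support that, because the direction depends on positive correlation. Positive correlation is the natural expectation for one person rating the same 16 symptoms every two to three days, but it remains an assumption.

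2. **The section speaks of an effect size and names no p-value, alpha or interval for Tau-U.** This is partly right. Phase contrasts and an omnibus test do imply testing, but no threshold decides anything. The 95% intervals mentioned for the other secondary outcomes are a separate matter and are not affected.

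3. **The conclusion does not rest on Tau-U alone.** This stands. Systematic visual analysis comes first, baseline lengths are randomised, and the three-tier design is replicated five times. A reader might infer that the efficacy evaluation has no protection at all, or that the authors left out a safeguard because they believed the sentence. The documents show neither. These features support the overall inference, but they do not correct the Tau-U standard error.

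4. **Efficacy is a secondary objective in a feasibility study.** This stands, and it limits the severity. A spurious signal would contribute to a decision that also weighs completion and adverse events, and the next step would be a randomised trial.

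None of the four makes the sentence about autocorrelation correct.

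**Conclusion.** The statement is wrong and should be corrected. If successive RPQ readings are positively correlated, the calculator's tests reject a true null too often and any intervals from it are too narrow. For an assumed lag-1 correlation of 0.2 to 0.6, the false-positive rate at a nominal 5% is about 9–32% per participant and 10–29% for the omnibus, with or without the baseline-trend correction. Standard errors are understated by a factor of roughly 1.2 to 1.9.

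These figures rest on an AR(1) process, no trend, and a two-sided 5% level that the protocol does not state. This is a point to fix, but it does not undermine the trial. The primary feasibility outcomes are untouched, and Tau-U remains usable as a description of overlap between phases.

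**What to change.** 1. Delete the words that credit Tau-U with controlling autocorrelation.
2. Report the lag-1 correlation of the RPQ residuals, pooled over participants, since six baseline readings are too few for a useful individual estimate.
3. Report Tau-U as a descriptive effect size, and do not rely on the online calculator's p-values or intervals.
4. Base any inference on a method that allows for serial dependence. Two options fit the design:
   - A randomisation test using the randomised baseline lengths. This works for the series, not for single participants: with three possible lengths, one participant's smallest p-value is 1/3. If each set of three participants receives each length once (an assumption, as block size is not stated), there are 6^5 = 7,776 arrangements, which is ample.
   - A multilevel model with AR(1) errors pooled over participants.

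Multiplying the Tau variance by (1+r)/(1−r) is a tempting shortcut, but it over-corrects, most of all with six baseline readings. At r = 0.6 the multiplier is 1.6/0.4 = 4.0, while the simulated uncorrected variance ratios are 1.663² = 2.8 (nA = 6), 1.825² = 3.3 (12) and 1.851² = 3.4 (18). Rejection then falls to about 0–3%.

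The cost is a wording change and some analysis code on data already being collected, with no extra visits or participants. The downside is wider intervals and fewer significant single-case contrasts.
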